#### Criteria for discontinuing or modifying allocated interventions {11b}

Patients will be informed of their freedom to leave the study at any time, for any reason, and without any consequences. The patient data that have been collected up to that moment will be included in the analysis (intention-to-treat approach), unless they require the research team to delete it. Reassignment of patients between the study arms is not contemplated. As an exception, if one patient who is assigned to the PCT-VR arm rejects using VR, then it would be randomized to one of the other two conditions. For those declared as eligible, no harmful effects have been identified so far for the psychological treatments included in the study.

#### Strategies to improve adherence to interventions {11c}

Patient’s treatment compliance will be monitored by attendance to therapy sessions and homework completion. The schedule of therapy sessions from all arms can be adjusted to the individual patient’s needs in order to facilitate therapy completion. Treatment adherence will be monitored by the specialized therapist delivering the treatment, in close contact with the research team.

On the other hand, with regard to treatment integrity and therapists’ adherence to the type of therapy delivered, different strategies will be implemented. Before the start of treatment, differentiated training workshops will be developed for each type of treatment to provide therapists with specific training in the protocols for the therapy formats used in the study. Within the trial, therapy sessions will be audio recorded (as reflected in the informed consent) for facilitating session-by-session supervision with senior members of the team. They will evaluate the performance of the therapists in order to maximize their adherence to the relevant manual and ensure that therapy is beneficial for its recipients. Finally, from the therapy protocols of the three conditions of the study, a scale will be developed to assess the adherence of the therapists to the corresponding protocol. For the CBT arm of the study, therapist adherence will be assessed using the revised cognitive therapy scale [39]. Because there are no pre-existing adherence or fidelity measures for PCT, a scale will be created to measure therapist adherence to this therapy arm. Two trained clinical graduate students blinded to the treatment conditions and trained to use the scale reliably will rate the audiotapes of 10 sessions of CBT, PCT, and PCT-VR. Inter-rater reliability and success at discriminating between the content of the CBT and PCT will be computed.

#### Relevant concomitant care permitted or prohibited during the trial {11d}

Concomitant psychotherapy is not permitted while participating in the intervention phase of the study. Antidepressant and other kinds of psychotropic medication are permitted during the trial, but the dosage will be recorded at baseline, end of therapy, and follow-up assessments.

#### Provisions for post-trial care {30}

No provisions for post-trial care are anticipated.

#### Secondary outcomes

General psychological distress will be assessed with the Clinical Outcomes in Routine Evaluation-Outcome Measure (CORE-OM) [42]. It is a 34-item self-report questionnaire for the assessment of subjective well-being, symptoms or problems, life functioning, and risk. It showed good psychometric properties which were preserved when Spanish adaptation was tested with a local sample [43]. This version will be used to assess the change in this study. The mean of the total scores will be compared as the change from baseline to post-treatment and 6-month follow-up assessments to test the statical significance. To measure the clinical significance, the same methods proposed for the BDI-II will be used. The short version (CORE-SFB) of 18 items will be used for session-to-session monitoring of the therapy process.

Symptoms of depression, anxiety, and stress will be evaluated with the Depression, Anxiety, and Stress Scales (DASS-21) [44]. This 21-item version of the DASS comprises seven items for each scale (depression, anxiety, and stress). The scores for each scale range from 0 to 21. There have been validation studies with the Spanish population finding satisfactory psychometric properties [45]. The main advantage of using the DASS-21 as a secondary measure is that it includes the assessment of other symptoms related to, but not equal to, depression. While anxiety and stress are expected to decrease with intervention, the primary outcome and the CORE-OM do not include specific items to assess stress and anxiety. The mean of the total scores for each scale will be compared as a change from baseline to post-treatment and 6-month follow-up assessments to verify statical significance. To gauge clinical significance, the same methods proposed for the BDI-II will be used.

The quality of the therapeutic alliance will be assessed with the Session Rating Scale 3.0 (SRS 3.0) [46]. It is composed of 4 items answered through a visual analog scale of 10 cm. They measure clients’ appreciation of the relationship with their therapist, agreement about the goals and issues discussed in the session, agreement with the method or approach, and global assessment of the session. The Spanish version obtained good levels of validity and reliability [47]. This measure will be used in each session, and its association with treatment outcome and modality will be analyzed. The mean of the total scores will be compared between treatment conditions for each session.

For diagnosing psychiatric disorders according to ICD-10, the Mini International Neuropsychiatric Interview (MINI) [48] will be applied. In this study, MINI is used for diagnosing inclusion (mild and moderate depression) and exclusion (major depression disorder, bipolar disorders, psychotic symptoms, etc.) criteria, as well as comorbid conditions (e.g., anxiety, eating, or personality disorders). Evaluators will conduct the MINI-based clinical interview before allocation and after treatment, and percentage of remitted patients will be compared across treatment conditions.

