#### Specific objectives

To assess the efficacy of an innovative VR-enhanced treatment modality of psychotherapy (PCT-VR) which has never been tested before. Differential outcomes will be considered not only in terms of statistical but also clinical significance and remission rates. In addition to the reduction of depressive symptoms, the change in psychological functioning, well-being, and satisfaction with the services provided will be assessed.To evaluate the efficacy of PCT for mild-to-moderate depression in young adults, a psychotherapeutic approach with some supporting evidence for a variety of disorders and conditions but still insufficient to be considered efficacious for depression.To verify the good levels of efficacy shown by CBT in the treatment of depression. This might be relevant in the light of the controversy about its efficacy in recent times [9].To gauge the contribution of the therapeutic alliance in the outcomes of the three different treatments being tested. The rationale for focusing on this variable relies on the fact that, as mentioned above, the therapeutic alliance is the best predictor of success across treatment modalities [31]. In addition, engagement (which is a factor of the therapeutic alliance) is purported to be crucial in the treatment of young adults and targeted by the nature of two treatment modalities being tested out in this trial (PCT and PCT-VR).

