### Interventions

#### Intervention description {11a}

Specific therapy protocols for the three treatment conditions of the study (CBT, PCT, and PCT-VR) have been developed. These three treatments will follow the same format: a maximum of 10 individual 1-h sessions, with one or two booster sessions at about 3 months after the tenth session. The protocols are not standardized since they are based on personalized case conceptualization. In both PCT and PCT-VR, the construction of self and others will be explored with the RGT; but while in the former, only 2D diagrams will be used (paper); in the latter, this will be done with EYME, in an immersive VR environment for each patient. A video with a brief illustration of the use of EYME in the treatment can be found at https://www.youtube.com/watch?v=aGOOo8p7EfM. Also, a brief description of the RGT procedure which will be applied in these two treatment conditions follows.

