## Assignment of interventions: allocation

### Sequence generation {16a}

Participants will be randomized to one of three arms in a 1:1:1 ratio, stratified by health center. Assignment will be conducted with computer-generated random block sizes of 3 or 6, masked from the study staff.

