## Statistical methods

### Statistical methods for primary and secondary outcomes {20a}

Intention-to-treat analyses (i.e., using outcomes from all randomized participants) will be performed for the main outcomes. Linear mixed models will be used to analyze and to compare treatment effects for the three treatment conditions (CBT, PCT, and PCT-VR). Baseline measurements, gender (coded as woman/male/not-binary), age, and clinical variables will be entered in the model as covariates. Pairwise comparisons will be used to test the hypothesis that PCT will lead to better outcomes than CBT and that PCT-VR will result in better outcomes than PCT. For all the analyses, effect sizes will be calculated.

In addition to the statistical significance, the proportion of patients who attain clinically significant improvement on the outcome measures will be calculated and compared between treatment conditions. The clinically significant improvement will be determined considering the proposal of Jacobson and Truax. For them, two conditions must be met: reliable change (reliability of pre-to-post difference in scores not being produced by chance) and clinically significant change (post-treatment scores lying in the normal instead of the clinical range). To test the differences in frequencies between the treatment conditions, a chi-square test will be applied.

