### Methods for additional analyses (e.g., subgroup analyses) {20b}

The inclusion of CORE-OM will permit to assess the degree of therapeutic change with regard to psychological distress, psychosocial functioning, and suicide risk. Also, the application of CORE-SFB and SRS 3.0 in each session will allow to assess the change experienced in psychological distress and therapeutic alliance as a function of the number of sessions and the percentage of change session by session. We will conduct growth mixture modeling based on these weekly assessments to identify distinctive patterns of change and evolution of the therapeutic alliance. If several patterns can be identified, we will perform mixed linear models and repeated-measure analyses of variance to compare patients’ characteristics in each pattern, and we will identify possible associations between change in psychological distress and therapeutic alliance scores. Then, we will consider using multinomial logistic regression to compute predictive models for the patterns from patients’ characteristics. Also, we could use hierarchical linear regression to establish the power of each pattern to predict treatment outcomes. Subgroup analyses by gender will be explored to check if there are significant differences in the therapy course. Secondary analyses will explore the potential mediator or moderator role of the cognitive measures obtained by the RGT, especially those measures related with cognitive conflicts. Finally, if the results of the trial support our main hypotheses, a complementary protocol for qualitative analyses of therapy sessions’ verbatim will be issued in due time with the goal of exploring the change mechanisms.

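### Comparing alliance scores between arms at each session gives 10 to 30 correlated comparisons with no overall contrast named and no correction stated, so the chance of a false-positive session is well above 5%

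*Protocol article*

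**What the plan says.** All references are to the Protocol article.

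- **Outcomes {12}, Secondary outcomes.** The SRS 3.0 is completed at every session. Two analyses are given: "This measure will be used in each session, and its association with treatment outcome and modality will be analyzed", and then "The mean of the total scores will be compared between treatment conditions for each session".
- **Intervention description {11a}.** Each arm has "a maximum of 10 individual 1-h sessions, with one or two booster sessions at about 3 months after the tenth session".
- **Sequence generation {16a}.** "Participants will be randomized to one of three arms in a 1:1:1 ratio, stratified by health center".
- **Statistical methods {20a}.** Linear mixed models will compare the three arms, with baseline measurements among the covariates. "Pairwise comparisons will be used to test the hypothesis that PCT will lead to better outcomes than CBT", and likewise that PCT-VR will do better than PCT. The Background and rationale also expects PCT-VR to do better than CBT, but {20a} does not list that pair.
- **Additional analyses {20b}.** "We will conduct growth mixture modeling based on these weekly assessments", to find patterns of change and of alliance.
- **Specific objectives.** One aim is "To gauge the contribution of the therapeutic alliance in the outcomes of the three different treatments being tested".
- **Schedule of assessments (Table 1).** The SRS is marked only for the intervention sessions. It has no baseline value.

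For the SRS, the article gives no significance level, test, correlation between sessions or multiplicity rule. The 0.1 one-sided level under Sample size {14} belongs to the BDI-II calculation.

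**The concern.** The article does not leave the between-arm analysis of this secondary outcome open. It sets the session as the unit of comparison, and that produces a family of tests with no member designated as the answer on alliance.

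This matters because alliance has a role in the trial's argument. It is the subject of a specific objective, and greater engagement is the stated reason why PCT-VR should outperform the other arms. If any one of ten or more sessions reaches nominal significance, it can be cited as support, and nothing fixed in advance says which session should count.

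There is a second, separate issue. Ten sessions is a maximum and no imputation is planned ({20c}). A comparison made within one session uses only those who attended it and answered. If patients with a poor alliance tend to leave, and do so unequally across arms, late sessions compare selected groups. A multiplicity correction would not cure that.

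**Working it through.** The plan states no error rate or number of tests for the SRS, so there is no figure of its own to reproduce.

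**Inputs from the article.** Three arms, hence three possible pairs; two pairs named in {20a}; at most 10 sessions plus one or two boosters; 75 patients per arm; dropout of 5% in the sample size and 35% cited from the literature in the Background.

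**Assumed, because not given.** Two-sided 0.05 per test; between-session correlation from 0 to 0.8; no true difference.

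**Step 1. Number of comparisons.**

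- One three-arm test per session: 10 × 1 = 10
- Two named pairs: 10 × 2 = 20
- All three pairs: 10 × 3 = 30 (with two boosters, 12 × 3 = 36)

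**Step 2. Bound if all tests were independent**, 1 − 0.95^k:

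- k = 10: 40.1%
- k = 20: 64.2%
- k = 30: 78.5%
- k = 36: 84.2%

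These overstate the error, because sessions share patients and pairs share arms.

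**Step 3. Simulation with correlated sessions.** 75 per arm, 10 sessions, equal correlation between any two sessions, attendance falling at random to 65% by session 10, 3,000 runs per setting. Chance of at least one significant session:

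| Between-session correlation | 0 | 0.3 | 0.5 | 0.7 | 0.8 |
|---|---|---|---|---|---|
| All three pairs | 72.7% | 66.7% | 57.3% | 47.2% | 42.5% |
| Two named pairs | 62.2% | 56.7% | 47.4% | 37.8% | 35.3% |
| One three-arm F test | 40.8% | 35.4% | 29.9% | 24.1% | 20.8% |

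The Monte Carlo standard error is at most sqrt(0.5 × 0.5 / 3000) = 0.9 percentage points.

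**Step 4. Sensitivity.**

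- With 5% instead of 35% attrition, results move by no more than about 6 points. The lowest is 19.0% (F test, correlation 0.8) and the highest 74.3% (three pairs, correlation 0).
- With correlation decaying over sessions (adjacent correlation 0.3 to 0.9, 35% attrition), three pairs give 71.5% down to 40.2% and the F test 37.3% down to 19.9%.
- At an equal correlation of 0.9, three pairs give 32.5% and the F test 15.1%, the lowest uncorrected figure found.
- With two boosters, three pairs reach 78.9% at correlation 0 and 50.6% at 0.7 (35% attrition).
- Attrition was random in these runs, so they say nothing about selection bias.

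**Step 5. Precision of a session average.** With full attendance and equal correlation ρ, the standard error of a ten-session mean relative to one session is sqrt((1 + 9ρ)/10): 0.61, 0.74 and 0.85 at ρ = 0.3, 0.5 and 0.7. This is a gain if the arm difference is constant over sessions.

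**Step 6. What an average would lose.** The Intervention description says PCT-VR differs from PCT mainly in sessions 3 and 10. If an effect on alliance were confined to those two, the ten-session average would hold 2/10 = 0.2 of it. The test statistic would be 0.2/0.61 = 0.33 to 0.2/0.85 = 0.24 of that from a single affected session. A mean over sessions 3 and 10 keeps the full effect, with a relative standard error of sqrt((1 + ρ)/2), that is 0.81 to 0.92 for ρ = 0.3 to 0.7.

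**The case against.** **The sentence is an outcome definition, not a test.** It stands under Outcomes {12}, the BDI-II text has a similar form, and {20a} assigns linear mixed models to primary and secondary outcomes. Session contrasts taken from such a model would satisfy it. This stands in part: separate attenders-only tests are inferred, not stated. But the {20a} model adjusts for baseline, which the SRS does not have, so it cannot be applied to the SRS as written. Session contrasts from any model would still be 10 to 30 comparisons with none designated.

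**Other alliance analyses are planned.** This is true. However, growth mixture modelling looks for latent patterns and is not an arm contrast, and the association with modality has no stated contrast. Neither replaces the per-session comparison.

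**Session-level comparison has a design rationale.** This stands. The VR component is concentrated in sessions 3 and 10, and an all-session average alone could dilute its effect. The fix must keep a session-specific test.

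**A correction may be in an analysis plan that is not shown.** Also true. The point is limited to what this article fixes: the session as the unit of comparison.

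**A stronger inference.** A reader might infer that a chance finding is more likely than not. The documents do not support that. It needs all three pairs tested at 0.05 with an equal between-session correlation below about 0.6 to 0.7, or the two named pairs with a correlation below about 0.45. The article gives neither the correlation nor the level, and {20a} names only two pairs. With one three-arm test per session, the chance stays near 40% at most for ten sessions.

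**Conclusion.** The point holds in a limited form. The stated analysis implies 10, 20 or 30 correlated comparisons, with no overall alliance contrast named and no correction stated in this article. With no true difference and an assumed two-sided 0.05 per test, the chance of at least one false-positive session is roughly 20% to 75% for between-session correlations of 0 to 0.8. It was at least 15% in every uncorrected scenario examined.

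A reader might also conclude that late-session comparisons are biased by differential dropout. The article gives no attendance by arm, a patient with fewer than ten sessions need not have dropped out, and no size can be put on such bias. It is a risk only if sessions are analysed separately.

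This is a secondary outcome and the BDI-II conclusion is unaffected. The change is still worth making, because alliance carries interpretive weight in this trial and the better analysis is readily available.

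**What to change.** Replace the per-session sentence under Secondary outcomes with the following:

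- **Model.** One linear mixed model on all SRS total scores, with fixed effects for arm, session, arm-by-session and health center, and a patient random effect. There is no baseline SRS term. State whether booster sessions are included.
- **Alliance contrast.** The session-averaged arm difference for each planned pair. {20a} names PCT versus CBT and PCT-VR versus PCT; if PCT-VR versus CBT is also intended, as the Background suggests, list it.
- **VR-specific contrast.** For PCT-VR versus PCT, also name the mean difference over sessions 3 and 10, or a joint arm-by-session test.
- **Error control.** With the two pairs in {20a} this leaves three tests. At 0.05 each, their family-wise error is at most 3 × 0.05 = 15%, so state the level and either a testing order or an adjustment such as Holm.
- **Other sessions.** Show means with confidence intervals in a plot, without p-values.

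The model keeps the early scores of patients who later leave and is valid if missingness depends on observed data. That is a weaker assumption than attenders-only comparisons need, but it is still an assumption.

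The cost is a change of wording. The data are already to be collected and mixed models are already planned. The downside is that no formal claim can be made for a session that was not named in advance.

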### Other measures

#### Consumer Reports Effectiveness Scale (CRES-4) [49]

It consists of four items designed to evaluate whether patients are satisfied with the therapy they have received and if it has been perceived as effective or not. The total score is intended to reflect the degree of satisfaction with the treatment received. The mean of the total scores for each treatment condition as assessed at follow-up will be compared.

#### Life Satisfaction Scale [50]

The patient is asked to rate on a Likert scale of 10 points the overall degree of satisfaction with life at the present moment. This single item has shown to have an acceptable reliability, and it is theoretically consistent. The mean of the total scores will be compared across treatment conditions as a change from baseline to post-treatment and 6-month follow-up assessments.

#### Client change interview [51]

This semi-structured interview was created to assess the changes produced throughout therapy, the useful and adverse effects of interventions from the patient’s perspective. Patients are asked about the positive and negative changes they have experienced with the intervention. Questions are also asked about the attribution of such changes, and their probability of occurrence without intervention. It is administered after completion (post-treatment), and its function is to identify both changes that patients are aware of (in their own words) and adverse effects (too often neglected in psychotherapy research). All these aspects might go unnoticed with standardized questionnaires.

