Several clinical guidelines point out that psychotherapy is the first-line treatment to address mild-to-moderate depression in teenagers and adults, and pharmacological treatments are reserved to more severe and complex cases that do not respond to psychotherapy [6]. Research about different treatments for depression highlights that psychological therapies are effective and contribute to preventing more severe and recurrent depressive disorders [7]. Regarding the theoretical orientation of the psychological treatments applied, the literature shows that cognitive behavioral therapy (CBT) is the approach that has published more studies, obtaining thus more prestige [8], whereas others claim that its efficacy is diminishing [9]. Indeed, current evidence is not conclusive about signaling one particular form of psychotherapy as clearly more effective than the others, and some reviews consider also other well-established psychological treatments [10], there is a lot of room for improvements (i.e., more than 40% do not respond, only 30% achieve a complete recovery, and relapse rates are high).

On the other hand, some research has pointed out some other factors than therapeutic orientation. Khan et al. [11] claimed that getting the patients engaged in an active therapeutic program was crucial, especially if we consider a dropout rate of 35% [12]. As the engagement in therapy relies on the preferences and attitudes of each patient, therapists might benefit from the availability of a variety of evidence-based psychotherapeutic alternatives. Along these lines, Cuijpers et al. [13] emphasized the importance of personalizing therapies. Another factor that supports the need for adapting the treatment to the patient’s preferences and characteristics is the therapeutic alliance (including the agreement on the therapy tasks), acting as the best predictor of success in virtually any therapy modality [14].

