## Data collection and management

### Plans for assessment and collection of outcomes {18a}

All data from questionnaires will be gathered using an automatized system (e.g., Qualtrics™), even if participants are physically accompanied by their therapist or evaluators when completing the forms. To ensure data collection in every stage (baseline, therapy monitoring, and follow-ups), a number of quality control procedures will be used, such as providing participants with warnings whenever a question has been left blank to minimize the frequency of missing answers, notifying the research coordinator indicating that a participant is not eligible (e.g., the score in the BDI-II is above 28), and warning the research team if a patient is at risk (e.g., suicidal ideation) or a participant has not completed the questionnaire.

Screening interviews will be conducted in synchronous videoconference settings by psychology graduates specifically trained in the MINI by researchers of the team. Interviewers will enter data in the data system right after the interview whereas participants will be emailed individualized links to complete baseline questionnaires (BDI-II, CORE-OM, and DASS-21). All diagnoses will be supervised by the trial coordinator to ensure validity and homogeneity throughout the recruitment process. Then, to monitor the psychotherapy process, participants will also be emailed individualized links to complete the CORE-SFB just before each session, and the SRS 3.0 for the therapeutic alliance at the end. The post-treatment assessment consists of all the baseline measures, including the MINI interview which will be performed, whenever possible, by the same evaluators who carried out the baseline interview and again supervised by the trial coordinator. In addition to these instruments, the change interview will also be conducted by a researcher who did not have previous contact with the patient. With respect to follow-up measures, participants will be emailed (and reminded by telephone, if necessary) an individualized link to the questionnaires containing the same assessment protocol as in previous time points plus the CRES-4, for evaluating treatment satisfaction.

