### Plans to promote participant retention and complete follow-up {18b}

Patients will receive extensive information about the study setup, and the importance of completion of the treatment and the follow-up assessments will be stressed. With respect to psychotherapy, whenever a session is missed, the therapist will contact the patient to re-schedule the session and to identify the reasons for non-attendance to prevent missing future sessions. Patients are allowed to abandon the study at any time. The trial coordinators will inquire about the reasons for withdrawal while respecting their right to do so. In addition, they will be encouraged to complete the follow-up questionnaires. This will be important to the intention-to-treat analyses in an attempt to maximize the number of participants in each study arm. All patients will be reminded throughout the study to fill out the questionnaires by individualized emails as well as by therapists and outcome assessors. Throughout the follow-up period, the trial coordinator will check the responses and, if necessary, contact the patients for completion of their follow-up.

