#### Adverse event reporting and harms {22}

As indicated previously, adverse events, if any, are expected to be minor due to the nature of the interventions. Regarding the intervention with VR, measures will be taken to prevent the occurrence of side effects arising from the use of VR devices that can be annoying or temporarily affect normal activity. Under certain conditions, the use of these devices can produce mild discomfort related to dizziness, nausea, headache, or eye dryness in some users. These discomforts can arise at any time throughout and beyond the therapy sessions. Currently, the factors that increase the risk of these unwanted reactions are known [53], and we will take measures to prevent them:
The virtual environments will be designed to be stable so that any movements will arise only from the user’s action.These movements will be reduced to a minimum by using techniques such as teleportation, which reduces the side effects of the simulation to almost zero.The participants will be instructed to immediately report any side effects to the therapist, who will interrupt the session until the complete disappearance of any nuisance.At the end of each session, participants should remain seated for a few minutes until it is clear that side effects are not present. If there is any discomfort, even to a small degree, they will remain seated, accompanied by the therapist until their complete recovery.

Apart from this VR-related dizziness, no harmful effects have been identified in the psychological treatments included in the study. However, at the end of each session, the presence and type of adverse events reported by the participants or observed by the investigators will be systematically recorded. The frequency, severity of all the detected harms, and causal relation to the treatment interventions will be analyzed and reported in forthcoming publications.

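### Harm recording is at risk of bias: it relies on attended sessions, prompts for symptoms only around VR, and gives no stated route for logging harms in patients who stop early

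*Protocol article*

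**What the plan says.** Harms reach the record by two routes.

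- **Session recording.** The section on adverse event reporting and harms {22} has "at the end of each session, the presence and type of adverse events reported by the participants or observed by the investigators" recorded systematically. This is not restricted to one arm.
- **The Client Change Interview.** Its section says: "It is administered after completion (post-treatment), and its function is to identify both changes that patients are aware of". The same sentence gives it the second function of finding adverse effects, and the section warns that standardised questionnaires can miss such things. Table 1 schedules it at post-treatment only. Under the plans for assessment {18a}, "the change interview will also be conducted by a researcher who did not have previous contact with the patient".

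Within the list of VR measures, section {22} adds two steps: "The participants will be instructed to immediately report any side effects to the therapist" and "At the end of each session, participants should remain seated for a few minutes until it is clear that side effects are not present". No counterpart is described for PCT or CBT.

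For patients who withdraw, the retention section {18b} has the coordinators ask why, and adds that "they will be encouraged to complete the follow-up questionnaires". Therapists also ask the reason for a missed session. None of these contacts is tied to adverse-event recording or to the interview.

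Section {22} promises an analysis of the frequency, severity and causal relation of the harms detected. It names no between-arm comparison.

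**The concern.** Two features of the stated schedule can distort the harm record.

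**Leavers.** A patient who stops because therapy made things worse attends no further session, and so produces no further end-of-session record. That patient may also never reach the interview. The questionnaires offered instead measure symptoms. They are not described as asking about side effects or whether the patient blames the treatment.

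**Unequal prompting.** The VR discomforts named in section {22} (headache, nausea, dizziness, dry eyes) are common complaints that can occur in any arm. The record depends on what patients report and what staff observe. Extra prompting and observation are described only around VR, and patients, therapists and researchers are unblinded (section {17a}). PCT-VR against PCT is the contrast meant to show what VR adds (trial design {8}), so unequal prompting matters most there.

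The record carries weight because the protocol plans no data monitoring committee and no audits, and describes PCT-VR as untested. Harms that were not asked about at the time cannot be recovered by a later analysis plan.

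**Working it through.** The plan states no harm rate, so there is no figure of its own to reproduce. The checks below show scale only.

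**1. How many patients are affected**

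Inputs: 75 per arm, 225 in total, 5% dropout (sample size {14}); 35% dropout (background {6a}: "especially if we consider a dropout rate of 35" per cent, a figure from the literature and not this trial's planning value).

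Formula: number stopping early = n × d.

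- d = 0.05: 75 × 0.05 = 3.75 per arm; 225 × 0.05 = 11.25, about 11 in total.
- d = 0.35: 75 × 0.35 = 26.25 per arm; 225 × 0.35 = 78.75, about 79 in total.

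**2. Understatement if leavers contribute nothing (worst case)**

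Let p_c be the share of completers with a harm and p_l the share of leavers. Both are assumptions. The true share is (1 − d) × p_c + d × p_l. The share seen among completers is p_c.

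| d | p_c | p_l | True share | Seen in completers | Shortfall |
|---|---|---|---|---|---|
| 0.05 | 0.10 | 0.30 | 0.095 + 0.015 = 0.110 | 0.10 | 1 point |
| 0.35 | 0.10 | 0.30 | 0.065 + 0.105 = 0.170 | 0.10 | 7 points |
| 0.05 | 0.10 | 0.50 | 0.095 + 0.025 = 0.120 | 0.10 | 2 points |
| 0.35 | 0.10 | 0.50 | 0.065 + 0.175 = 0.240 | 0.10 | 14 points |
| either | 0.10 | 0.10 | 0.100 | 0.10 | 0 |

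These are upper limits for the assumed rates, because events up to the last attended session are in fact recorded.

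**3. What this does to a difference between arms**

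Take p_c = 0.10 and p_l = 0.30 in both arms.

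- Equal dropout: the true difference is 0 and the difference seen is 0.
- Dropout of 5% against 35%: the true difference is 0.170 − 0.110 = 0.06, and the difference seen in completers is 0.

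A between-arm distortion from this source therefore needs dropout, or harm among leavers, to differ by arm. The documents give no figure for either.

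**4. Unequal prompting**

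Let p be the true share with a symptom, equal in both arms, and s the chance that it is recorded. The spurious difference is p × (s_VR − s_other). All values are assumptions.

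- p = 0.10, s = 0.9 against 0.6: 0.10 × 0.3 = 0.03, or 6.75 against 4.5 patients of 75.
- p = 0.10, s = 0.9 against 0.75: 0.10 × 0.15 = 0.015.
- Equal s: 0.

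VR is used mainly in sessions 3 and 10 (intervention description {11a}), so the extra prompting applies to few sessions.

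**The case against.** Much can be said for the plan.

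- **The core recording is common to all arms.** End-of-session recording and the interview are not arm-specific, and the VR steps are presented as prevention. The article does not say how events are elicited in PCT or CBT, so some prompting there cannot be excluded. This narrows the asymmetry. It does not remove it, because only VR has a described instruction and observation period.
- **The interview may already cover leavers.** The words about completion may simply name the post-treatment time point. Neither Table 1 nor section {18a} restricts it to patients who finished therapy. This stands, and the figure of 79 depends on the narrower reading.
- **Leavers are not invisible.** The follow-up questionnaires include the BDI-II, DASS-21 and CORE-OM, and the CORE-OM has a risk domain. They can show deterioration. The CORE-SFB tracks distress before each attended session, and reasons for leaving are asked. What is missing is narrower: a question on side effects or attribution, and a link from the answers to the adverse-event log.

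A reader might also draw two stronger inferences, which the documents do not support.

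- **That a between-arm harm comparison is biased.** No such comparison is specified, and under-recording that is equal in every arm does not by itself create a false difference.
- **That PCT-VR patients attend more sessions and so have more chances to register an event.** All arms share one format, "a maximum of 10 individual 1-h sessions, with one or two booster sessions". The introduction expects more engagement with VR, and the discussion credits PCT with and without VR. No session counts by arm are predicted.

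**Conclusion.** The concern holds as a risk of bias, not as a demonstrated bias. Followed as written, the schedule would prompt for the same everyday symptoms unequally in an open trial. Beyond asking why they left, it states no route for logging harms that early leavers attribute to treatment.

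About 11 patients are affected at the planning dropout. The upper figure of about 79 rests on two assumptions: the literature dropout rate, and an interview confined to completers. The percentage-point effects shown above rest on assumed harm rates and recording probabilities. The documents fix neither the size nor the direction of any difference between arms. This is a minor point and a cheap improvement.

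**What to change.** 1. Add one short symptom checklist, identical in all three arms, to the Session Rating Scale link that patients already complete at the end of each session. It would cover the VR-type discomforts and worsening mood. Leave the VR safety measures as they are. This equalises prompting but reaches attenders only, so the second change is also needed.
2. Offer the interview's adverse-effect questions at the coordinator's existing contact about withdrawal, and include them in the questionnaires sent to leavers. Log the answers as adverse events.
3. State that the Client Change Interview applies to every randomised patient at the post-treatment time point, whether or not therapy was completed.

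The cost is a few extra items and a short script for a contact that already takes place. The downside is a higher count of mild events in PCT and CBT. Some leavers will still decline to answer.
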